**Abstract**

**Introduction** High prevalence of non-communicable diseases is a worldwide public health challenge resulting in morbidity and mortality, as well as significant hospitalization rates and huge personal and societal costs. Several trials in the last decades have demonstrated that preventive strategies (i.e. lifestyle modification) can delay or prevent the development of Type 2 diabetes Mellitus (T2DM) in high-risk individuals. We present the protocol for a randomised controlled trial to assess the effectiveness of a theory-driven Guided Self-Determination (GSD) intervention designed to improve health-care services, prevent chronic diseases, and deliver better risk-factor management among people at risk of developing T2DM or with manifest T2DM.

**Methods and analysis** We will recruit 308 participants from general practice into an intervention involving general practitioners (GPs) and registered nurses using GSD versus standard care GP consultation only. The primary outcome will be changes in the Patient Activation Measure (PAM-13). As secondary outcome measures, we will evaluate the effect of the intervention on BMI, waist circumference, HbA1c, Problem Areas in Diabetes (PAID-5) scale, WHO Well-Being Index (WHO-5), Quality of life (QOL Health Item - 2 items), EQ-5D, HLS-EU-Q12 and Perceived competence diabetes scale (PCDS – 4 items). The effect of the intervention will be measured after 3, 6 months and 12 months and estimated using linear mixed effects regression for continuous outcomes and mixed effects logistic regression and generalized estimating equations for binary outcomes. We will conduct qualitative interviews among patients, health care professionals and user representatives to further inform the evaluation of the program. We will analyse the qualitative data by using thematic analysis. In addition, we will examine intervention fidelity.

**Ethics and** **dissemination** Ethical approval has been obtained from the South-Eastern Norway Regional Committee for Medical and Health Research Ethics (2019/28/REK sør-øst A). The trial is registered in ClinicalTrials.gov (ID: NCT04076384).

**Strengths and limitations of this study**

- This study has the potential to extend the knowledge of the effects of delegated independent tasks and nurses’ roles in a team-based approach in general practice on identifying need for follow-up.
- The study will facilitate adequate self-management support by using a theory-driven Guided-Self-Determination intervention in the follow-up of people with high-risk of or with manifest type 2 diabetes mellitus.
- The study will embed qualitative interviews with patients, healthcare professionals and user representatives to gain insight into their experience when participating in the study.
- A limitation is that the assignment of general practices is limited to practices with trained nurses in Guided-Self-Determination that can use the team-based person-centred intervention as support for their nursing follow-up consultations.
- We will not evaluate long-term effects (i.e. >12 months).

**INTRODUCTION**

High prevalence of non-communicable diseases is a worldwide public health challenge resulting in morbidity, and mortality, as well as significant hospitalization rates and huge personal and societal costs. Among chronic conditions, diabetes prevalence ranks very high, expected to reach 592-642 million people by 2035-2040 ^1,2^. One in ten adults is estimated to have diabetes by 2040. Type 2 diabetes (T2DM) is associated with various and serious complications such as cardiovascular disease and kidney disease ^2^. Together with risk factors such as high blood pressure and tobacco use, high blood glucose has been identified as the third largest risk factor for diabetes related mortality globally ^2^. It is estimated that 1 in 12 of all-cause adult deaths globally are attributable to diabetes ^3^. Being overweight, obese, or having an unhealthy lifestyle are strongly linked to T2DM regardless of genetic risk ^4^. Thus, a major concern for public health is to halt the rise in obesity in the general population to reduce the risk of developing diabetes ^5^. In 2014, the most recent year for which global estimates are available, more than one in three adults over 18 years of age were overweight and more than one in ten were obese ^6^. To prevent obesity and to delay serious complications among people with manifest T2DM, adequate primary care services are essential. Several trials have demonstrated that lifestyle modifications can prevent or delay the development of T2DM in high-risk individuals ^2,7,8^. Lifestyle intervention aiming at weight reduction, a healthy diet and increased physical activity in high-risk individuals has a long-lasting effect in the prevention of T2DM ^8,9^. Moreover, lifestyle interventions can prevent or delay further development among people with manifest T2DM. The DIRECT study found that an intensive lifestyle follow-up program in the early stages of T2DM, supported by registered nurses and dieticians in general practice led to diabetes remission in 46% of participants in the intervention group compared to 4% in the control group ^7^.

Assessing people’s skills and knowledge is essential in a person-centred and individual approach to problem solving for people at risk of chronic disease or with manifest chronic disease. Interventions should focus on these aspects ^10^. To assess people`s ability to engage with their own health behaviour might be measured by using a patient activation measurement instrument (PAM) ^11^. The degree of activation and engagement might contribute to better self-management and overall better health outcomes ^12,13^.

A recent Norwegian study found that intensive individual-level intervention seems to be an important strategy in preventing T2DM ^14^. General practitioners (GPs) in Norway are in general overloaded with limited possibilities for more intensive follow-up of people at risk of or with chronic disease ^15^. The increasing workload in general practices is also reported in other countries ^16^. Further research to identify feasible strategies for the implementation of healthy lifestyle interventions for people at risk of or with manifest T2DM is important. Involvement of nurses in education and counselling of patients has shown to have positive effects on hospital admissions and mortality ^17^. Thus, team-based follow-up in primary care is a promising strategy to improve quality outcomes in a strengthened primary care system. However, a call for further studies on the use of multi-professional and team-based follow-up in Norwegian primary care is warranted ^18^. Especially, there is limited research on delegated independent tasks to nurses in general practice in Norway. Such studies conducted in the Norwegian context are important because nurses traditionally have had a less autonomous role in the care and follow-up of persons in general practice suffering from common chronic diseases such as diabetes compared to other Scandinavian countries ^19^.

The potential for improvements in patients’ attentiveness to medical treatment and better adherence to lifestyle change is unambiguous. A systematic literature review suggested that person-centred care may lead to significant improvements for the patients, but the implementation and relevant effects needs to be assessed in more studies ^20^. This study strives to improve the quality in health-care services in general practice by applying the team-based Guided Self-Determination intervention. Guided Self-Determination is a theory-driven counselling approach with the purpose to guide people and health care professionals through mutual reflection and activation ^21,22^.

We aimed to develop, test and evaluate a team-based Guided Self-Determination (GSD) intervention in general practice designed to improve patient activation and self-management among people with T2DM or at risk of developing T2DM. The effect of the intervention will be compared to standard care (GP consultation only) in terms of patient activation and self-management.

**METHODS**

We will undertake a randomised controlled trial (RCT) among people at risk of developing T2DM or with manifest T2DM to test the effect of the intervention using guidance from the Medical Research Council (MRC) framework for developing, testing and evaluating the GSD intervention as a team-based person-centred approach in general practice ^23^. We report our protocol using Standard Protocol Items: Recommendations for Interventional Trials (SPIRIT) checklist <https://www.spirit-statement.org/> ^24,25^.

**Trial population, eligibility criteria and recruitment**

We will identify people with increased risk of developing T2DM (by the Finnish Diabetes Risk Calculator ^26,27^ (FINDRISC) ≥ 15 or BMI ≥30) and those with manifest T2DM (by HbA1c ≥48 mmol/L) aged between 20-80 years to participate in the study. We will exclude people with severe somatic disease (i.e. severe cancer, severe heart failure, end stage renal disease), severe psychiatric diagnosis (e.g. severe depression, bipolar disorder, schizophrenia), or recorded cognitive deficiency (e.g. Down’s syndrome, Alzheimer’s disorder) or who do not write, speak or understand Norwegian. Separate trials will be performed for people with risk of developing T2DM and people with manifest T2DM.

*Sample size*

We performed power analysis based on the 13-items Patient Activation Measure (PAM-13) as the primary outcome (patients’ ability for self-management of one’s health or chronic condition) with a total score ranges from 0-100 (best) ^11^. Based on a previous study we expect a mean (SD) PAM-13 score at baseline of approximately 52 (14) ^11^. For either one of the participants at risk of developing T2DM or manifest T2DM, we estimated the required sample size to be 64 participants to detect a treatment effect of 7 points (0.5 SD) with 80% power and a two-sided 0.05 significance level. To account for possible dropouts, we will increase the sample to 77 (20% increase) in each group. Accordingly, we will need to include a total of 154 patients in each group (among people with risk of T2DM and with manifest T2DM), e.g n= 77 in the intervention with GSD and n= 77 in the GP follow-up only. We will recruit participants through a screening questionnaire handed out to persons in the waiting room at GP offices. The screening questionnaire will include questions about manifest diabetes in addition to the FINDRISC. According to Jølle et. al ^14,28^ the prevalence of elevated FINDRISC (≥15) among 47,694 adults in the third survey of the Nord-Trøndelag Health Study (HUNT3, 2006–08) was 11%. Thus, to identify at least 154 patients at high-risk of developing T2DM from a population with an estimated prevalence of elevated FINDRISC score of 11%, our screening population in general practice will need to include at least 1400 people (154/0.11). To include enough persons with manifest T2DM we will also identify people with T2DM through the medical records at the GP office and ask them if they want to participate.

**Adapting the intervention for use in general practice for people in risk of developing T2DM or with manifest T2DM**

We have previously developed and adapted routines for using GSD in the team-based person-centred follow-up program in general practice, and conducted feasibility studies to explore benefits and challenges using the person-centred GSD program among adults in different settings and formats ^29-33^. However, further adaption was needed to refine the program for use in a team-based follow-up program in a busy general practice context. Also, we adapted the intervention to include people at risk of developing T2DM. Through this adaptation process we learned that it was beneficial to reduce the total number of semi structured reflection sheets from the original program that we have used in a previous web-based intervention study ^30,31^. Thus, the intervention now consists of a stepwise approach with 1-4 consultations over 12 months (Fig. 1) and a more flexible use of reflection sheets considering the condition as well as each individual’s needs to reflect upon lifestyle modifications and problem-solving communication. To maintain quality in the use of GSD the nurses take part in a training program for advanced communication skills from the GSD program, life skills and self-management, supervised exercises, and a reading list.

*Figure 1 Overview of reflection sheets*

We will test the feasibility of the adapted intervention in one GP practice in Vestland county with ≥3 GPs and ≥1 nurse(s). Trained nurses and GPs will assess the patients’ individual risk profiles with scores over target level and refer a total of 10-15 patients to participate. GSD is a theory‐driven counselling approach ^22,34,35^. Originally, the GSD program comprised seven face-to-face consultations with 21 semi structured reflection sheets for people with type 1 diabetes. Reflection sheets and communication skills (mirroring, active listening and values clarification response) aim to guide patients and nurses through a mutual reflection, empowering the patient to become self-determined, achieve life skills and enhancing their self-management skills in living with a chronic disease. In the present study, trained GSD nurses in the intervention group will also involve the GPs in the team-based consultations.

The intervention will mainly be face-to-face consultations, however also telephone or video consultations might be considered if suitable in the follow-up. Between the consultations, the participants will fill in a set of reflection sheets using their own words and drawings to express and reflect on their experiences and difficulties with the management of their disease in daily life as well as to formulate behavioural goals and plans to achieve improved self-management. The nurses using GSD will also capture this in the structured consultations as well as report on this in the medical records after the consultations. Structured training by telephone, video or face-to-face meetings for the nurses is provided before the intervention starts as well as every month to ensure that the intervention is conducted according to protocol.

*Control:* The patients in the control group will receive usual care, follow-up with GP consultations only (without the use of GSD).

*Patient recruitment:*

We will conduct the study in four GP practices in Vestland and Viken counties with ≥3 GPs and ≥1 nurse(s). We will hand out screening questionnaires to people in the waiting room at the four GP practices. Only people who are listed as patients to the specific GPs` practices will be asked to answer the questionnaires.

*Data and methods:* We will randomise the patients into an intervention arm with team-based person-centred structured consultations (with a nurse using GSD to identify psychosocial and behavioural problems and improving patient-provider communication) versus standard care (GP consultation only) by computer generated numbers. The randomization sequences will be generated by an independent person using statistical software. We will begin enrolment of the first patient in the follow-up program in December 2019 and continue with participant recruitment for the intervention until baseline data collection have been fulfilled at all GP practices. The intervention is designed to evaluate a change in patient activation and self-management, in addition we will train the nurses in GSD, therefore blinding of the intervention is not possible. An internal pilot is carried out on the first ten patients entering the study ^36,37^. These patients will be included in the final analysis if appropriate. We will use the diabetes form in the electronic patient records for those with manifest T2DM to extract demographic and clinical data as well as questionnaire data to assess the effect of the intervention after three, six and twelve months.

*Primary outcome (table 1):* Patient Activation Measure (PAM-13). The PAM-13 instrument ^38,39^ capture patient's knowledge, skills, and confidence for self-management living with chronic conditions. It has 13 items with four response categories with scores from 1 to 4: “strongly disagree” (1), “disagree” (2), “agree” (3) and “agree strongly” (4). The item scores are transformed to a 0 to 100 scale (0 = lowest activation level, 100 = highest activation level). The manual suggests cut-off points to categorize patients into four levels of activation reflecting their engagement in health behaviour. Level 1 (0 - 47) indicates that the individual may not believe the patient role is important, level 2 (47.1 - 55.1) indicates that a patient lacks confidence and knowledge to take action, level 3 (55.2 - 67.0) indicates that a patient has started to engage in the recommended health behaviour, and level 4 (67.1 - 100) indicates that a patient is proactive concerning health and engages in many types of recommended health behaviour. PAM-13 has been translated to Norwegian, validated, and used in previous Norwegian studies ^11,40^.

*Secondary outcomes (table 1)*: BMI, waist circumference, HbA1c, Problem Areas in Diabetes (PAID-5), WHO Well-Being Index (WHO-5), Quality of life (QOL Health Item - 2 items), EQ-5D, HLS-EU-Q12 and Perceived competence diabetes scale (PCDS – 4 items). Moreover, we will record hospitalization events and number of GP’s consultations from the electronic patient records after the intervention is ended.

**Table 1.** Outcome measures.

| **Chronic disease** | **Primary outcome** | **Secondary outcomes** |
| --- | --- | --- |
| Risk of T2DM | Patient Activation Measure (PAM 13) – reduction of 5-10% | Weight reduction  Waist circumference reduction  Blood pressure reduction  Lifestyle adherence: physical activity >30 min/day  WHO Well-Being Index (WHO-5)  Quality of life (QOL Health Item - 2 item)  EQ-5D  HLS-EU-Q12 |
| Manifest T2DM | Patient Activation Measure (PAM 13) – reduction of 5-10% | Weight reduction  HbA1c reduction  Waist circumference reduction  Lifestyle adherence: physical activity >30 min/day  Blood pressure reduction  Adherence to medical treatment  Problem Areas in Diabetes (PAID-5)  WHO Well-Being Index (WHO-5)  Quality of life (QOL Health Item - 2 item)  EQ-5D, HLS-EU-Q12  Perceived competence diabetes scale (PCDS– 4 items)  We will record hospitalization events and number of GP’s consultations from the electronic diabetes form. |

*Statistical analysis:* The effect of the intervention will be measured after 3, 6 months and 12 months as difference in change in mean values of the outcomes. The effect will be estimated using linear mixed effects regression models and reported as regression coefficients with 95% confidence intervals for continuous outcomes. For binary outcomes we will use mixed effects logistic regression and report the effect as odds ratios (OR) with 95% confidence intervals. In case of differential drop-out we will perform sensitivity analyses with adjustment for characteristics which differ between those who complete the follow-up and those who are lost to follow-up. If follow-up data for binary outcomes seem to be missing completely at random we will also apply generalized estimating equations (GEE) with log-link to estimate risk ratios (RR). We will use two-sided tests with 5% as the significance level for all models.

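### Three rules around the fixed main models (pilot inclusion, drop-out sensitivity analysis, GEE risk ratio) depend on the data and lack usable criteria

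*Protocol*

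**What the plan says.** The main analyses carry no condition. In the Protocol, Methods, Statistical analysis paragraph: "The effect will be estimated using linear mixed effects regression models and reported as regression coefficients with 95% confidence intervals for continuous outcomes", which covers the primary outcome, PAM-13. For binary outcomes, all secondary: "For binary outcomes we will use mixed effects logistic regression and report the effect as odds ratios (OR) with 95% confidence intervals".

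Three further rules are conditional:

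- **Pilot patients** (Methods, Data and methods paragraph): "An internal pilot is carried out on the first ten patients entering the study", followed by "These patients will be included in the final analysis if appropriate". The same paragraph says of the design, "therefore blinding of the intervention is not possible".
- **Drop-out** (Statistical analysis): "In case of differential drop-out we will perform sensitivity analyses with adjustment for characteristics which differ between those who complete the follow-up" and those who do not.
- **Risk ratios** (Statistical analysis): "If follow-up data for binary outcomes seem to be missing completely at random we will also apply generalized estimating equations (GEE", with a log link.

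For none of the three does the protocol give a criterion, a time of decision, or a statement that whoever decides is blind to outcomes.

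**The concern.** Each rule leaves a choice open until data are available, and each has its own weakness.

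(a) The pilot rule acts on the primary analysis set. With no criterion, and with allocation known to patients and staff, ten enrolled patients could be kept or removed after their PAM-13 scores are known.

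(b) The drop-out rule does not define differential. If it means unequal rates between arms, equal rates with different reasons for leaving would not set it off. When it does run, it adjusts for observed characteristics selected because completers and drop-outs turned out to differ on them. Such an adjustment still assumes missing at random (MAR). In a trial of patient activation, loss that depends on unseen activation is a plausible threat, and this analysis cannot examine it.

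(c) Observed data can refute missing completely at random (MCAR) but cannot establish it. A check that finds nothing would therefore admit an unweighted GEE whose risk ratio is generally valid only if MCAR is true.

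**Working it through.** **The plan's own figure.** Inputs from the Sample size paragraph: difference 7, SD 14, two-sided 5%, 80% power. Normal approximation: 2 × (1.960 + 0.842)² × 14²/7² = 62.8, so 63 per arm. The t-test gives 63.8, so 64 as stated. 64 × 1.20 = 76.8, so 77 per arm, 154 per trial and 308 in total. These reproduce.

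**(a) Pilot.** 10/308 = 3.2%; 10/154 = 6.5% if all ten fall in one trial. In that case removal leaves 72 per arm. With an assumed 20% loss, 77 × 0.8 = 61.6 and 72 × 0.8 = 57.6 per arm, and t-test power for 7 points is about 79% and 76%. The loss of power is small; the issue is discretion over who is analysed.

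**(b) Drop-out rule.** Assume about 17% loss (26 lost, 128 completers in one trial). A 5% t-test comparing the two groups on a baseline characteristic has this power:

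| True gap (SD) | Power |
|---|---|
| 0.2 | 15% |
| 0.3 | 28% |
| 0.4 | 46% |
| 0.5 | 64% |

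A deliberately severe illustration for PAM-13, with every input assumed: no true effect; 17% loss in both arms; loss tied to the unseen part of the outcome in opposite directions by arm (log-odds 1 per SD); correlation of 0.5 with baseline; one follow-up visit analysed by ANCOVA; 4,000 simulated trials. Mean bias is about 3.6 points, half the 7-point target, and the false-positive rate is about 42%. A test of unequal arm rates fires in 2.6% of runs and a completer-versus-lost baseline test in 4.9%. Under true MCAR the figures are 2.9% and 5.0%. Neither reading of the trigger sees this mechanism.

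**(c) Risk ratio.** Assumed inputs: 77 per arm; a binary outcome such as the activity target, met by 0.55 (intervention) and 0.42 (control) at 6 and 12 months; within-person dependence from a logistic random intercept with SD 2; loss after 6 months; GEE with independence working correlation. True RR = 0.55/0.42 = 1.31.

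The random intercept implies these chances of meeting the target at 12 months:

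| Arm | Met at 6 months | Not met at 6 months |
|---|---|---|
| Intervention | 0.727 | 0.334 |
| Control | 0.647 | 0.256 |

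*Pattern 1.* The intervention arm loses 10% of those who met the target at 6 months and 30% of those who did not; the control arm loses 20% at random.

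- Intervention loss: 0.55 × 0.10 + 0.45 × 0.30 = 19%, against 20% in control.
- Observed intervention proportion: (0.55 × 0.727 × 0.9 + 0.45 × 0.334 × 0.7)/(0.55 × 0.9 + 0.45 × 0.7) = 0.465/0.81 = 0.574.
- RR = 0.574/0.42 = 1.37, about 4% too high.

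*Pattern 2.* The control arm is mirrored, losing 30% of those who met the target and 10% of those who did not.

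- Control loss: 0.42 × 0.30 + 0.58 × 0.10 = 18.4%.
- Observed control proportion: (0.42 × 0.647 × 0.7 + 0.58 × 0.256 × 0.9)/(0.42 × 0.7 + 0.58 × 0.9) = 0.324/0.816 = 0.397.
- RR = 0.574/0.397 = 1.45, about 11% too high.

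*Standardising under MAR.* Weighting the retained patients' 12-month proportions back to the full 6-month distribution gives 0.55 × 0.727 + 0.45 × 0.334 = 0.55, and likewise 0.42 in control, so the RR returns to 1.31.

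*Detection, by simulation.* A Fisher test of drop-out against 6-month status, pooled over arms, fires in about 31% of runs in pattern 1 and 3 to 4% in pattern 2. Within the intervention arm alone it fires in a little over half. A test of arm rates fires in about 3%.

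**The case against.** The case for leaving the text alone is substantial, and much of it stands.

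- A reader might infer that the key analyses, or the effect measure reported, depend on the results. The documents do not support this. The PAM-13 model and the odds ratio are unconditional, the risk ratio is an addition, no binary outcome is primary, and the stated condition is the missingness pattern rather than the effect estimate.
- The MCAR condition shows restraint: the model valid under MAR is the main one, and GEE is confined to cases where its stricter assumption looks plausible. That is fair, but a condition that cannot be verified does not give the protection intended.
- The drop-out in (c) depends on an observed 6-month value, so it is MAR and spares the main mixed models. With an SD of the log RR of about 0.19, the bias is between a quarter and half of one standard error. The lowest detection rate needs mirrored patterns and a pooled check, and the protocol prescribes no particular check.
- Differential can be read as completers differing from drop-outs, since the sentence goes on to that comparison. Equal arm rates would then not silence it. What remains is that the word is undefined and the adjustment is limited to observed variables.
- A reader might also see a contradiction in the Abstract, which lists "mixed effects logistic regression and generalized estimating equations for binary outcomes" without the condition. That is abbreviation in a summary.
- Missing-data detail may sit in an SAP that is not shown. The point here is therefore not absent detail. It is that the rules the protocol does state are conditional, and an SAP that made them unconditional would depart from them.

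**Conclusion.** The point holds in this limited form. The primary and main secondary models are fixed and sound on this score. Of the three rules, only the pilot clause can change the primary analysis set, by at most 10 of 308 patients (3.2%), or 10 of 154 (6.5%) in one trial. This assumes that the ten are randomised patients. The drop-out clause has an undefined trigger and, even when triggered, cannot address loss that depends on unseen outcomes; the 3.6-point figure shows that blindness under severe assumed inputs and is not a forecast. The MCAR clause admits a risk ratio that could be about 4% to 11% too high (1.37 to 1.45 against 1.31) under the assumed patterns. That bias concerns only a supplementary analysis of secondary binary outcomes and should not be carried over to PAM-13. The rules should be corrected before outcome data are examined, but they do not undermine the design.

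**What to change.** 1. State that every randomised patient, internal pilot included, enters the primary analysis in the arm allocated.
2. Run one pre-specified drop-out sensitivity analysis on PAM-13 whatever the observed drop-out. One option is delta-adjusted imputation: lower the imputed intervention-arm values in steps up to the 7-point target and report the tipping point. If covariate adjustment is kept as well, name the covariates in advance.
3. Remove the MCAR condition. Derive the risk ratio under MAR, either by standardising the mixed logistic model or by GEE after multiple imputation using arm, baseline and earlier outcomes.

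The cost is a few sentences and a little programming, with no change to recruitment or data collection. The one drawback is that pilot patients count even if delivery was still being refined, which may slightly dilute the estimated effect.
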